### Eligibility criteria for patients

In order to be eligible to participate in this study, patients should be: Children aged 7–18 years old and diagnosed with NAFLD: Referring to the Expert Consensus on the Diagnosis and Treatment of Non-Alcoholic Fatty Liver Disease in Children (13), the clinical diagnostic criteria need to meet 1–4 of the following, and any 1 of (5) or (6): (1) except for other pathological obesity; (2) in addition to the clinical manifestations of the primary disease, some patients may have non-specific symptoms and signs such as weakness, dyspepsia, vague pain in the liver area, hepatosplenomegaly, etc.; (3) overweight, obesity (centripetal obesity), elevated fasting glucose, lipid metabolism disorders, hypertension, and other metabolic syndromes; (4) alanine aminotransferase (ALT) is elevated more than 1.5 times the upper limit of normal value (60 U/L) and persists for more than 3 months; (5) liver imaging technique to diagnose hepatic steatosis; (6) histological changes in liver biopsy meet the pathological diagnostic criteria of fatty liver disease. Patients will not be eligible if they do not agree to participate or participate in other health intervention programs.

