### Outcome

The primary outcome are serum biomarkers such as alanine aminotransferase (ALT) and gamma-glutamyl transferase (GGT). Second outcomes are: aspartate aminotransferase, and liver imaging (liver ultrasound and magnetic resonance imaging), BMI, waist-to-hip ratio and quality of life. In addition, socio-demographic characteristics such as age, gender, and ethnicity will be recorded. All outcomes were measured at baseline, week 4, week 16, week 24, week 36, and week 48 to determine the trajectory of change in outcome variables over intervention process.

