### Statistical analyses

First, after eliminating the questionnaires that did not meet the requirements, all data will be organized and quantified and then entered the statistical software in pairs for analysis. Then statistical description of the data will be done, including descriptive statistical analysis of patients' general information, the mean and standard deviation will be used to describe the measurement data that conformed to normal distribution. Finally, statistical inferences will be made and *t*-test, ANOVA. The effect of the intervention on NAFLD w analyzed using McNemar's test for paired categorical data and χ^2^ or Fisher's exact test for independent categorical data, as appropriate. Changes in continuous variables will be analyzed using paired Student *t*-test. Statistical significance will be set at *P* < 0.05. Using analysis of covariance we evaluated whether baseline variables predicted changes in liver fat content and ALT during 6 months of treatment.

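### Change in the continuous outcomes, including primary ALT and GGT, is assigned to a paired t-test, which does not test the difference between the randomised arms

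*Protocol article*

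**What the plan says.** The trial randomises children to two parallel arms, 40 in each. The Outcome section makes ALT and GGT primary and schedules all outcomes at baseline and weeks 4, 16, 24, 36 and 48.

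The Statistical analyses section then makes four statements about testing:

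- **General inference:** "Finally, statistical inferences will be made and", followed only by *t*-test and ANOVA. No outcome, time point or contrast is attached.
- **NAFLD as a categorical outcome:** the tests are "McNemar's test for paired categorical data and χ^2^ or Fisher's exact test for independent categorical data, as appropriate".
- **Change in continuous outcomes:** "Changes in continuous variables will be analyzed using paired Student" *t*-test.
- **ANCOVA:** "Using analysis of covariance we evaluated whether baseline variables predicted changes in liver fat content and ALT during 6 months of treatment". No treatment term is mentioned.

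Two other places bear on the point. Under Eligibility criteria for patients, one of the required criteria is that "alanine aminotransferase (ALT) is elevated more than 1.5 times the upper limit of normal value (60 U/L) and persists for more than 3 months". Under Intervention, Table 1 gives the control arm diet and exercise education at hospital visits and a monthly review with feedback.

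**The concern.** A paired t-test asks whether the mean change in one set of children differs from zero. Children in this design are not paired across arms, so the test cannot say whether the intervention arm changed more than the control arm. That difference is what the trial was randomised to estimate.

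The distinction matters here because the document itself gives two reasons to expect ALT to fall in both arms. Selection on a raised ALT brings some regression to the mean, and control families receive education and regular review. If a significant paired test in the intervention arm were read as evidence of effect, the web-based model could be declared effective while adding nothing to routine care.

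**Working it through.** **What each test targets.** Let *s* be the mean change shared by both arms and θ the extra change due to the intervention.

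- Intervention-arm paired test: the null hypothesis is *s* + θ = 0.
- Between-arm test of change: (*s* + θ) − *s* = θ, so the null hypothesis is θ = 0.

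With θ = 0 and *s* ≠ 0, the paired test rejects at its power to detect *s*. The between-arm test rejects at its nominal 5%, whatever *s* is.

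**Inputs from the protocol article (Sample size section).** 32 evaluable per arm and two-sided α = 0.05. The plan's allowance for losses reproduces: 32 / (1 − 0.20) = 40 per arm. How 32 was derived from the stated effect size is a separate question and is not used here.

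**Input that is assumed.** The document gives no SD of change and no expected control-arm fall. The shared fall δ = *s* / SD of change is therefore set at 0.2, 0.3, 0.5 and 0.8.

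**Formula.** The paired t statistic follows a noncentral t distribution with n − 1 degrees of freedom and noncentrality λ = δ√n. With n = 32, √32 = 5.657, df = 31 and the two-sided 5% critical value is about 2.04. The table gives P(|T| > critical value) when θ = 0.

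| δ (assumed) | λ at n = 32 | Paired test significant, n = 32 | Paired test significant, n = 40 |
|---|---|---|---|
| 0 | 0 | 5.0% | 5.0% |
| 0.2 | 1.13 | 19.5% | 23.5% |
| 0.3 | 1.70 | 37.6% | 45.7% |
| 0.5 | 2.83 | 78.2% | 86.9% |
| 0.8 | 4.53 | 99.2% | 99.9% |

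**Reading the two arms side by side does not repair this.** If the rule were intervention arm significant and control arm not, its chance under θ = 0 is p(1 − p), with p from the n = 32 column:

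- δ = 0.2: 0.195 × 0.805 = 0.157
- δ = 0.3: 0.376 × 0.624 = 0.235
- δ = 0.5: 0.782 × 0.218 = 0.170

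The maximum is 0.25, at p = 0.5.

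**Regression to the mean alone.** This was simulated with 5,000 trials per setting, 32 per arm and no treatment effect. Entry was above a cut-off at the population mean or 1 SD above it, and the assumed baseline-to-follow-up correlation ran from 0.95 to 0.7. The intervention-arm paired test was significant in 11% to 92% of trials. The between-arm test of change was significant in 4.7% to 5.4%. The simulation selects on a single value, so it will tend to overstate the effect of a criterion that requires persistent elevation.

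**The case against.** **The plan may intend a between-arm test.** A plain t-test listed apart from the paired one can be read as the independent-samples test. Other sections suit an arm comparison: the sample size is per group, analysts are blinded to allocation, and the Discussion promises an intention-to-treat analysis. This stands in part. A reader might infer that the trial throws away its randomisation, or that shared improvement is certain to be credited to the intervention. The document does not support that, because it nowhere says that efficacy will be judged on a within-arm P value. But the listed t-test and ANOVA are tied to nothing, whereas the sentence on change is specific and names the paired test.

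**McNemar's test.** A reader might also infer that NAFLD status has no between-arm test. That is wrong: the same sentence names the χ² or Fisher's exact test for independent data. What is left there is to say which of the tests judges the intervention.

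**Regression to the mean.** ALT must stay raised for more than 3 months, which reduces regression to the mean compared with a single screening value, though it does not remove it. No entry threshold applies to GGT, so for GGT the mechanism is at most indirect. Shared improvement through control-arm education remains possible for both outcomes.

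**The error rates are not properties of the plan.** This stands. They rest on assumed shared falls and on decision rules that the document does not state.

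**A journal article leaves detail to a fuller document.** That would excuse silence on covariates or time points. It does not cover a named method that fails to address the randomised comparison.

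**Conclusion.** The point holds in a limited form. The only test explicitly tied to change in continuous outcomes, and so to ALT and GGT, is a within-arm test, and no between-arm analysis is clearly assigned to either. Improvement common to both arms can therefore be credited to the intervention if the paired tests are used as the test of effect.

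The size is conditional. False-positive rates of about 20%, 38% and 78% correspond to assumed shared falls of 0.2, 0.3 and 0.5 SD of change, with 32 per arm and no treatment effect. They are illustrations, because the document does not fix the shared fall. The direction of the error does not depend on these assumptions: any non-zero shared change raises the paired test above 5% and leaves the between-arm test at about 5%.

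**What to change.** In Statistical analyses:

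1. State that the test of the intervention for ALT, GGT and the other continuous outcomes is a between-arm comparison adjusted for the baseline value. Either ANCOVA with a treatment term or a mixed model for repeated measures with arm-by-visit terms would serve. Report the estimated difference with a 95% CI.
2. Label paired t-tests as descriptive.
3. For NAFLD status, keep the χ² or Fisher's exact test already named as the between-arm test, and label McNemar's test as descriptive.
4. Tie the listed t-test and ANOVA to a stated outcome and contrast, or remove them.

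The scale of analysis, the time point and any further covariates are for the sponsor to choose. The cost is wording only, since baseline and five follow-up measurements are already planned.

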### Sample size

Sample size estimation will be performed using Professional Association for SQL Server (PASS) 2014 software for grasp degree analysis (Power Analysis). The mean effect size of the lifestyle intervention on the improvement of ALT indicators (Effect size) was estimated to be −1.35 according to the Meta-analysis of the clinical study conducted by Utz-Melere et al. (14, 15). The sample size required will be 32 study subjects per group by power analysis in reaching 80% effectiveness, using a two-tailed test with a test level of 0.05. Based on a 20% failure rate, this part of the study required 80 subjects, 40 in each group.

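### No baseline-adjusted comparison of the arms is planned for ALT and GGT, although baseline values are collected

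*Protocol article*

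**What the plan says.** All references are to the Protocol article.

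- **Outcome**: ALT and GGT are the primary serum markers. All outcomes are measured at baseline and at weeks 4, 16, 24, 36 and 48, so a baseline value of each marker is scheduled for every child.
- **Statistical analyses**, inference: the sentence starting "Finally, statistical inferences will be made and" goes on to list t-test and ANOVA, without saying what is compared. For change, "Changes in continuous variables will be analyzed using paired Student" t-test.
- **Statistical analyses**, covariance: "Using analysis of covariance we evaluated whether baseline variables predicted changes in liver fat content and ALT" over 6 months of treatment. This looks for predictors. It is not described as an estimate of the treatment effect.
- **Statistical analyses**, normality: "the mean and standard deviation will be used to describe the measurement data that conformed to normal distribution". The condition is attached to description. No measurement scale is named for inference.
- **Sample size**: an effect size of −1.35, 32 per group at 80% power and two-sided 0.05, and 40 per group after a 20% allowance for loss. No SD, correlation or difference in U/L is given.

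**The concern.** With 32 to 40 children per arm, chance differences in baseline ALT or GGT between arms can be sizeable. A comparison of follow-up values alone ignores them. A comparison of change scores over-corrects for them whenever the slope of follow-up on baseline is below one. ANCOVA with baseline as covariate estimates that slope from the data, so it removes the imbalance and also reduces the residual variance. The article already names the method and already collects the covariate, but uses the two together only for a secondary question. What is at stake is precision in the primary comparison. Validity is not: the t-test on change held its type I error at about 5% in simulation.

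**Working it through.** **1. The article's own figure.** The normal approximation for two means gives n = 2(1.96 + 0.84)² / 1.35² = 15.68 / 1.8225 = 8.6, so 9 per group (10 with the exact t). The stated 32 is not reproduced; it corresponds to a standardised difference of about 0.71. The allowance for loss does reproduce: 32 / 0.8 = 40. I use 32 per arm below because it is the stated number of analysable children.

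**2. Expected direction.** With equal variance σ² at both times and correlation ρ, the variance of a change score is 2σ²(1 − ρ). The ANCOVA residual variance is σ²(1 − ρ²). Their ratio is (1 + ρ)/2, or 0.80 at ρ = 0.6. If instead follow-up equals baseline plus independent error, the slope is one, the change score is already efficient, and ANCOVA gives up only the degree of freedom spent on the slope.

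**3. Simulation, proportional variation.** From the article: 32 per arm, two-sided 0.05, entry only above 60 U/L. Assumed: log-normal baseline ALT with median 80 U/L before the entry limit, log-SD s from 0.4 to 0.7, log-scale correlation 0.6, follow-up error log-SD s√(1 − 0.6²) = 0.8s, and a true ratio of 0.70. Each test compares the two arms.

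| log-SD | t-test on change, U/L | ANCOVA, U/L | Gain from adjustment | ANCOVA, log scale | Further gain |
|---|---|---|---|---|---|
| 0.4 | 93% | 98% | 5 | 99% | 1 |
| 0.5 | 78% | 91% | 13 | 94% | 3 |
| 0.6 | 59% | 76% | 17 | 83% | 7 |
| 0.7 | 44% | 61% | 17 | 71% | 10 |

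Repeat runs move individual entries by up to about 3 points. Most of the gain comes from adjustment, not from the change of scale.

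**4. Simulation, additive variation.** With an effect of 20 U/L and error SD 30 U/L, the t-test on change has 73–75% power and ANCOVA in U/L about 1 point less. Log change has 59–62%, and the log scale costs 11–16 points.

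**5. Reading.** Baseline adjustment gains 5 to 17 points in one setting and costs about 1 in the other. The log scale gains 1 to 10 points or loses 11 to 16, depending on facts the article does not give.

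**The case against.** The strongest reply is that this is a condensed article, that a fuller plan may specify the model, and that no shortfall is shown. On the last point the reply stands. At the article's effect size, 1.35 × √(32/2) = 5.40, and Φ(5.40 − 1.96) exceeds 0.999. At half that effect, 2.70 − 1.96 = 0.74, giving about 77%. It is also true that every size in the simulation rests on assumed variances and correlation. But the article does allocate methods, and it gives ANCOVA a different job, so the point is about a stated choice and not only a silence.

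Three stronger readings are tempting and are not supported:

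- *The markers will be analysed on the raw scale, at a substantial loss of power.* The article names no scale, and a t-test can be run on log values. The direction of any loss depends on whether variation is proportional or additive.
- *The entry rule causes the problem.* ALT must be "elevated more than 1.5 times the upper limit of normal value (60 U/L) and persists for more than 3 months", with no upper limit, and this does add skewness under a log-normal model. The power gap does not come from it. At log-SD 0.5, raw against log change is 78% against 92% with the limit and 72% against 87% without. GGT has no entry limit at all.
- *The arms are never compared.* A paired t-test alone would compare times within an arm. However, t-test and ANOVA are also listed with no comparison named, so a between-arm test may be intended.

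**Conclusion.** The point holds as an improvement, not as a demonstrated error. The article plans no baseline-adjusted comparison of the arms for ALT or GGT while using ANCOVA for another purpose. Under proportional variation with correlation 0.6 and a 30% reduction, adjustment is worth about 5 to 17 points of power at 32 per arm; under additive variation it costs about 1. The simulation is set up for ALT. For GGT the same reasoning applies, but its size depends on a correlation the article does not give. Severity is low: type I error is sound and the article's own effect size leaves ample power.

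**What to change.** In Statistical analyses, state that the primary analysis of ALT, and likewise of GGT, compares the arms by ANCOVA of the follow-up value with the baseline value of the same marker as covariate, or by a repeated-measures model over the scheduled visits with baseline as covariate. Report the adjusted difference with a 95% confidence interval. Keep the paired t-test, if wanted, as a description of change within each arm.

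If existing data or a blinded look at the pooled values show right skew with variation proportional to level, prespecify the log scale and report the ratio of geometric means with its interval. Otherwise stay in U/L.

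The cost is one or two sentences. No extra measurement, visit or child is needed. With the log option, the effect would be reported as a percentage difference instead of in U/L.

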### Ethics approval and consent to participate

This study protocol will be conducted at the study site only after obtaining review permission from the hospital administration where the study participants will be enrolled. The investigator must obtain informed consent from the participant and minimize the participant's exposure to other risks. Before the start of the study, the investigator introduced himself or herself and fully informed participants of the content and purpose of the study so that they were aware of the behaviors they might be asked to cooperate with and the amount of time they would spend in the study. The investigator informed participants that the study would not provide them with any realistic benefits, but also no disadvantages or risks; participants were informed that all recorded material would be used for research purposes only. Participants participated in the study anonymously in a WeChat group, where each person was required to change their name (replaced by a serial number) after joining the group. Participation was voluntary and participants could opt out of this study at any time. Verbal informed consent will be obtained from the participant before the start of the formal interview. The real names of the participants will be not used in the data and study reports; instead, numbers will be used to identify the participants. This study was registered on ClinicalTrials.gov (NCT05527938).

## Discussion

NAFLD is currently the most prevalent liver disease in the world, increasing the risk of cirrhosis and hepatocellular carcinoma, and contributing to the development of type 2 diabetes, cardiovascular disease, and chronic kidney disease (17, 18). BMI remains an important risk factor for NAFLD in children and young adults, and adipose tissue dysfunction contributes to the pathogenesis of NAFLD (19). General healthy eating advice and physical activity are recommended to promote weight loss in pediatric NAFLD. However, lifestyle interventions, be it general caloric restriction diets or low-fat or low-carbohydrate diets with or without increased physical activity, are frequently afflicted with low compliance and high drop-out and relapse rates in children and adults (20–22). In this study, we will implement the web-based intervention to provide more social and peer support to the affected child and family to improve their compliance with the intervention.

This current study has several strong features. Firstly, life-style interventions are the first step in managing children with NAFLD (14). The current studies have focused on promoting lifestyle changes in children with NASH by providing some education and advice to children and their families to improve the histological features of NASH and lose weight. As a previous systematic review mentioned, there is significant heterogeneity in study design quality, sample size, duration, outcome measures, and treatment interventions in RCTs for children with NAFLD. There is also a lack of effective and well-established lifestyle intervention programs to explore improvement in NAFLD. In addition, to our knowledge, web-based studies are currently being applied in adult NAFLD, providing web-based online training for those unable to attend face-to-face or group education (23). However, compared to adults, the child population is less sensitive to the Internet and adherent. Then, interventions for the entire population of children with NAFLD were not appropriately graded according to the severity of the disease, much less individualized for the different levels of intervention. Therefore, we used an adaptive strategy through Internet technology to implement individualized interventions according to each child's disease severity.

There are also some limitations that need to be addressed. Firstly, we estimate that there will be an attrition rate of ~10% of children who enroll in the study, mostly due to financial issues or time constraints. To minimize the effect of the biases, we will conduct the analysis on an intention-to-treat basis. It is important to consider that although this study will be conducted in the hepatobiliary ward of a specialist women's and children's hospital in Shaoxing, Zhejiang Province, this may lead to limitations in the findings. However, we are conducting a formative evaluation throughout the implementation of the project to explore which interventions or environmental factors may hinder or contribute to the effectiveness of this project at different stages of implementation to facilitate global replication.

